### Sample size calculation

As a type 2 hybrid effectiveness-implementation study, this study has two primary outcomes – fidelity to the blood pressure assessment protocol and effectiveness of the protocol. Type 2 hybrid studies can be powered on either primary outcome [34] given that the primary outcomes belong to separate samples and different interventions. Thus, this study is powered to detect effectiveness of the clinical intervention (changes in mean systolic blood pressure comparing control with intervention periods). To detect a conservative difference in mean systolic blood pressure of 5 mmHg between patients under the intervention versus control periods, with 85% power and alpha = 0.05, assuming a standard deviation (SD) in systolic blood pressure of 20 mmHg (SD computed from population-based data of adults in India and USA [35, 36]) we would require a sample of 506 patients across all clinics, not accounting for the design effect [37]. Assuming an intra-class correlation coefficient of 0.01, three steps, and nine study clinics over 15 months, we estimated a design effect of 3.2 [37]. After applying the design effect, 1640 patients are required, amounting to 46 patients with HIV and elevated blood pressure during the study period who are seen at each of three steps per clinic, which corresponds to an average of 184 patients seen annually per clinic. Because the smallest clinic in our sample serves > 300 patients with HIV and hypertension monthly (1725 patients seen monthly; ~20% with hypertension), we anticipate sufficient power to test our primary effectiveness hypothesis.

### Statistical methods

#### Overview

The statistical analyses are described according to implementation outcomes derived from clinics (i.e., *adoption*,* implementation*, and *maintenance* of the blood pressure assessment protocol) and outcomes related to intervention impact (i.e., *reach*,* effectiveness*, and *effect maintenance* of the intervention). We will use the standard Hussey and Hughes model for analysis of stepped-wedge designs [38] which includes fixed effects for both interventions and time periods, and a random effect for sites. We will extend this model to account for non-normal outcomes, repeated measurements on participants, and to include key covariates for each RE-AIM outcome as described below. All outcomes, patient characteristics, and clinic characteristics will be summarized (both overall and by intervention status) using means and standard deviations for continuous variables (or median [IQR] if data are skewed) and frequency counts with percentages for categorical variables. Statistical differences between pre- and post-intervention and initiated versus delayed (control) clinics during each observation period will be examined. Contingent on the observed distributions, differences in categorical outcomes will be assessed using chi-square or Fisher’s exact tests, and differences in continuous variables will be tested using independent group t-tests or Wilcoxon rank-sum tests. *P*-values < 0.05 will be considered statistically significant. Following these analyses, the costing, cost-effectiveness, and budget impact analysis will be conducted and are described at the end of this section.

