#### Implementation outcomes analyses

To assess fidelity of the blood pressure assessment protocol (*primary implementation outcome*) we will examine the difference in percent of patient-visits with recorded blood pressure (1 = blood pressure measured; 0 = blood pressure not measured) between intervention and control clinics using mixed effects log-binomial regression. If the mixed effects log-binomial model fails to converge, we will use a generalized estimating equation (GEE) log-binomial model with exchangeable correlation structure and robust standard errors; if the GEE log-binomial fails to converge, we will use a GEE log-Poisson model [39, 40]. We will examine changes in blood pressure assessment between clusters (“horizontal”) and across periods (“vertical”) to evaluate heterogeneity in treatment effects by cluster and period, respectively. Between-cluster and between-period heterogeneity will be evaluated through an intervention by clinic interaction term.

Adaptation data recorded during the active intervention period will be examined using means and standard deviations (or median [IQR] if data are skewed) and frequency counts with percentages. Maintenance of blood pressure assessment by clinic staff will be examined by adding an interaction term between intervention exposure status (control vs. intervention) and implementation phase (i.e., research staff vs. clinic staff) to the model described for the primary implementation outcome. Means and standard deviations (or median IQR) will be used to summarize normalization process questionnaire [32] data at the beginning and the end of the maintenance period. Paired samples t-tests (or Wilcoxon rank-sum tests) will be used to compare normalization questionnaire scores at the beginning and the end of the maintenance period.

Exploratory analyses will examine exposure to the implementation strategies (e.g., > 80% of audit and feedback sessions received) and compare blood pressure assessment rates against that of clinics with lower exposure via the modeling approach for dichotomous outcomes previously described. Causal diagrams and latent variable modeling will also be considered as exploratory tools to examine mechanisms through which implementation strategies affect blood pressure assessment implementation.

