#### Effectiveness outcomes analyses

To assess *reach*, we will summarize participant-level indicators, including age, sex, blood pressure at enrolment, treatment for blood pressure at enrolment, and HIV history by clinic at the initial intervention visit. We will then estimate the percentage of patients with elevated blood pressure that receive the initial educational materials and lifestyle advice plus medication (numerator), from all patients identified with elevated blood pressure (denominator). Demographic and clinical characteristics between reached/not reached patients will be compared using chi-square / Fisher’s exact tests for categorical variables, and independent samples t-tests / Wilcoxon rank-sum tests for continuous variables.

To assess clinical impact of the intervention (*primary effectiveness outcome)*, we will examine differences in mean systolic blood pressure between intervention versus control clinics. We will estimate the effect of clinic-level intervention exposure (no intervention versus intervention by research staff) using mixed effects linear regression models. In addition to the standard stepped-wedge model outlined previously, we will include a random effect to account for correlation due to repeated measurements on participants. We will also include randomization strata, sociodemographic characteristics (age, sex, and immigration status), and clinical characteristics (prior treatment for hypertension, HIV regimen, CD4 count, and viral load) in our final multivariable model to obtain an adjusted estimate of the intervention effect.

The effectiveness analysis will use data from months 1–15 while censoring data from the first two months of intervention initiation (i.e., the transition period from control to intervention; see Table 1). This is to provide time for the intervention to impact patient behavior and medication initiation, thus giving time for blood pressure to be affected. We will follow an intention-to-treat approach in which data from individual patients will be analyzed according to the clinic intervention status at the time of measurement. Standard model diagnostic procedures will be used to evaluate model fit, and transformations will be applied (e.g., log transformation) as needed.

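### With a site intercept as its only clinic-level random effect, the fidelity model's standard error will be much too small if clinic levels vary from period to period

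*Protocol article*

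**What the plan says.** The Overview under Statistical methods adopts the standard Hussey-Hughes model, "which includes fixed effects for both interventions and time periods, and a random effect for sites", and then lists its extensions: "We will extend this model to account for non-normal outcomes, repeated measurements on participants, and to include key covariates for each RE-AIM outcome".

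For blood pressure, Effectiveness outcomes analyses adds one more term: "we will include a random effect to account for correlation due to repeated measurements on participants". That section also adds randomisation strata and covariates.

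For fidelity, Implementation outcomes analyses compares visits with a recorded measurement "between intervention and control clinics using mixed effects log-binomial regression". Only if that model fails to converge does the plan move to a "generalized estimating equation (GEE) log-binomial model with exchangeable correlation structure and robust standard errors", and then to a GEE log-Poisson model.

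Variation by clinic and period is treated as a separate question: "Between-cluster and between-period heterogeneity will be evaluated through an intervention by clinic interaction term".

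On cluster sizes, Study populations takes fidelity data from adults seen in the study triage room, and Table 3 uses all visits in months 1–15 except the two months after initiation. Sample size calculation puts the smallest clinic at 1725 patients a month. The size strata in Study design run up to 10000 a month.

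**The concern.** A lone site intercept says that two visits to the same clinic are equally correlated whether they fall in the same period or a year apart. If a clinic's true measurement rate shifts for its own reasons (staffing, equipment, patient flow), the model has nowhere to put the shift except the residual. For a binary outcome, the residual is fixed by the binomial variance and the number of visits. With thousands of visits per clinic-period it is close to zero, so the model treats a local shift as firm evidence about the intervention. More visits make this worse. A participant effect does not absorb such a shift, because the shift is shared by all patients of a clinic in a period.

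At stake is the co-primary fidelity result. Its interval could be far too narrow, and ordinary fluctuation between clinics could reach significance. The maintenance analyses reuse the same models, and the one for blood pressure draws its conclusion from whether a 95% interval excludes zero.

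**Working it through.** **Inputs from the article.** Nine clinics, three sequences of three, alpha 0.05, planning ICC 0.01, 46 patients per clinic per step for blood pressure, and 1725 patients a month in the smallest clinic.

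**Assumed, because the article gives no figure.** The share *s* of between-clinic variance that is period-specific (5 to 20%); the fidelity ICC ρ (0.01 to 0.05); baseline fidelity of 50% where a percentage-point scale is needed; equal cells over four periods. For visits per cell *m*, 1725 is one month at the smallest clinic. Three months there would be 3 × 1725 = 5175, so 5000 is shown as a larger case.

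**The plan's own cell size.** 1640 / (9 × 4) = 45.6, which gives 46 per cell over four periods. With ρ = 0.01, SD 20 mmHg and no period-specific variance, the Hussey-Hughes standard error is 1.687 mmHg. Power for 5 mmHg is then Φ(5/1.687 − 1.96) = 84.2%, close to the stated 85%. The unadjusted 506 does not reproduce at 85% (two-sided: 576). That is a separate matter and is not used here.

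**Formula.** Remove clinic and period means from the 9 × 4 intervention indicator. Its remaining sum of squares is 2.5 (0.3056 + 0.2222 + 0.3056 = 0.8333 per set of three clinics, times 3). With total variance scaled to 1, and cells large enough for the site effect to act almost as a fixed effect:

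- reported variance ≈ [(1 − ρ)/m] / 2.5
- true variance ≈ [(1 − ρ)/m + ρs] / 2.5
- ratio of true to reported SE: r = √(1 + mρs/(1 − ρ))
- type I error = 2[1 − Φ(1.96/r)]

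**Fidelity**

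| m | ρ | s | mρs/(1 − ρ) | r | type I error |
|---|---|---|---|---|---|
| 1725 | 0.01 | 0 | 0 | 1.00 | 5% |
| 1725 | 0.01 | 0.05 | 0.87 | 1.37 | 15% |
| 1725 | 0.01 | 0.20 | 3.48 | 2.12 | 35% |
| 1725 | 0.05 | 0.05 | 4.54 | 2.35 | 40% |
| 1725 | 0.05 | 0.20 | 18.16 | 4.38 | 65% |
| 5000 | 0.01 | 0.05 | 2.53 | 1.88 | 30% |
| 5000 | 0.05 | 0.20 | 52.63 | 7.32 | 79% |

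**Check by simulation under no effect.** The planned mixed log-binomial model with a site intercept only (1725 per cell, baseline 50%, 150 runs per setting) gave:

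- 3% with ρ = 0.05 and s = 0
- 35% with ρ = 0.01 and s = 0.20
- 57% and 69% with ρ = 0.05 and s = 0.10 and 0.20

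A five-period layout, with a linear model at the same cell size and s of 0.10 to 0.20, gave 22 to 68%.

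**Percentage-point scale** (1725 per cell; variances multiplied by 0.25). For ρ = 0.05 and s = 0.20, the reported SE is √(0.25 × 0.95/1725/2.5) = 0.74 points, and the true SE is √((0.25 × 0.95/1725 + 0.25 × 0.01)/2.5) = 3.2 points. For ρ = 0.01 and s = 0.05, the figures are 0.76 and 1.0 points.

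**Blood pressure.** At m = 46, ρ = 0.01 and s = 0.20, mρs/(1 − ρ) = 0.093, so r is about 1.04 and type I error about 6%. At ρ = 0.05 and s = 0.20, it is about 10 to 11%. With 200 per cell and s of 0.10 to 0.50, simulation gave 9 to 16% at ρ = 0.01 and 16 to 43% at ρ = 0.05.

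**With a clinic-by-period random effect added.** Simulated type I error was about 3 to 8% against a normal reference, and 1 to 4% against t on 7 df.

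**GEE fallback.** An uncorrected sandwich on nine clinics gave 10 to 15%, whatever the period-specific share. A t reference on 7 df reduced this to 6 to 9%. A bias-corrected sandwich was not run.

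**The case against.** The strongest reply is that every severe figure is conditional. The article states no period-specific share, fidelity ICC or baseline fidelity, and with no clinic-specific movement the planned model is correct. This stands, so the point must be put conditionally. However, zero movement is a strong assumption for a staff-dependent measure, and the plan itself intends to look for heterogeneity by clinic and period. That interaction test sits beside the primary analysis and does not correct its standard error.

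A reader might infer that both co-primary outcomes are seriously compromised. The documents do not support that: at the plan's own ICC and cell size, blood pressure type I error is about 6%.

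A reader might also infer that the plan commits to uncorrected robust standard errors. It says only that they are robust. A small-sample correction is the kind of detail an analysis plan may supply, and the GEE is used only on non-convergence. Its cluster-robust variance also largely absorbs period-specific variation, so the two weaknesses do not affect the same fit.

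The cell size is inferred too. 1725 is a monthly patient count, not a count of observed triage visits, and some months are dropped. Smaller cells soften the problem: 500 visits with ρ = 0.05 and s = 0.10 gave 31% in simulation.

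Finally, a false positive would usually be an apparent gain of a few percentage points. The article says equipment was lacking and is being supplied, so the real effect may be much larger and remain significant. Its interval would still be too narrow.

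**Conclusion.** The point holds for fidelity, conditionally. The article states the model, so this does not turn on a detail left to an unseen analysis plan. If 5 to 20% of between-clinic variance is period-specific, the fidelity standard error is about 1.4 to 4.4 times too small at 1725 visits per cell, with type I error of about 15 to 65% for an ICC of 0.01 to 0.05. The understatement grows with the number of visits. If clinic levels do not vary by period, there is no problem.

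For blood pressure the effect is minor as planned. It would matter if the ICC or the cells were larger, which continuous recruitment and repeated visits make possible. The GEE fallback is a secondary matter.

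The change should be made, but the documents do not show that the fidelity analysis will fail.

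**What to change.** Add a clinic-by-period random effect to the primary fidelity model and, for consistency, to the blood pressure model. State small-sample inference suited to nine clinics: a t reference on about 7 df (clusters minus two), Kenward-Roger for the linear model, and a randomisation test within the size strata as a check. If the GEE fallback is reached, use a small-sample-corrected sandwich (Kauermann-Carroll or Fay-Graubard) with a t reference.

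The cost in wording and code is small; the cost in precision is not always so. Intervals widen, and t on 7 df was conservative in simulation (1 to 4%). With 46 per cell and 10 to 20% period-specific variance, blood pressure power against a normal reference is 82 to 83% at the planned ICC of 0.01, but about 66 to 73% at 0.05. The extra random effect may also make the log-binomial model harder to fit, so the fallback should be settled at the same time.

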### Study design

 We employ a type 2 effectiveness-implementation hybrid study type to simultaneously test implementation strategies and a clinical intervention [22]. Specifically, we will evaluate the effect of the implementation strategies on guideline-concordant hypertension care practices in participating clinics, as well as the effects of the guideline-concordant care on patient blood pressure. For the evaluation, we employ a stepped-wedge, cluster randomized trial design. This protocol aligns with the Standards for Reporting Implementation Studies Statement [23] and with the CONSORT statement for reporting stepped-wedge, cluster randomized trials [24]. The study protocol is registered in ClinicalTrials.gov (NCT05846503).

We selected a stepped-wedge, cluster randomized trial design for three reasons. First, since the study has the potential to improve healthcare delivery, all participating clinics wanted to receive the intervention and this design ensures all clinics do. Second, this is an implementation study testing interventions under routine care conditions; as such, a sequential roll out of the proposed intervention allowed us to alter care for a proportion of clinics at a time. Finally, given the research and clinical resources available, rolling out the intervention in all clinics at the same time (i.e., cluster RCT) was not feasible; thus, a sequenced rolled out was preferred. These reasons outweighed the main limitations of the clustered randomized stepped wedge study design – selection bias and confounding due to temporal changes in clinical care concurrent with the intervention rollout [25].

Table 1 depicts the trial design, periods, and sequence allocation order. In our study, clinic was the unit of randomization. Clinics were stratified into three groups based on clinic population size, categorized by monthly patient head count as small (1000 to 3499), medium (3500 to 6999), and large (7000 to 10000). Clinics were then randomized via a computer-generated sequence to cross-over from the control to the intervention condition starting in Period 2 until all clinics crossed over to intervention. One clinic from each size stratum was randomly selected for each sequence. The study biostatistician ([name]) generated the randomization schedule and assigned clusters to sequences using SAS software, version 9.4 (SAS Institute Inc, NC USA). [name] enrolled the clusters.

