The allocation sequence began with an observation period where none of the clinics had neither received the implementation strategies nor rolled out the patient intervention (Period 1). In this period, we collected implementation and clinical data under the control condition. After the control period, clinics crossed-over to the intervention condition, three at a time based on their randomization sequence. To date, all nine clinics have-crossed over to the active intervention period which will run from study months 4–15 (Periods 2–5). Since this intervention was randomized at the clinic level and involves providing clinical care, blinding was not possible. For each step, clinics were notified one month in advance prior to initiation of the intervention.

At month 14, all clinics will initiate a two-month offboarding transition period (Period 5). Here, research staff will support clinic staff to ensure that implementation strategies continue to be executed, while also helping them to further integrate the blood pressure assessment protocol within routine care. From months 16–27, research staff will be withdrawn from clinics and a maintenance observation period will begin (see Table 1).

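### Unadjusted initiated-versus-delayed and pre/post tests at P < 0.05 ignore clinic clustering and calendar time, and a rank-sum test is named for paired scores; the co-primary models are unaffected

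*Protocol article*

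**What the plan says.** The Overview of the statistical methods first commits to the Hussey and Hughes stepped-wedge model, with period effects and a random clinic effect, extended for repeated measurements and non-normal outcomes. It then describes summary tables of outcomes and of patient and clinic characteristics, and adds: "Statistical differences between pre- and post-intervention and initiated versus delayed (control) clinics during each observation period will be examined". For categorical outcomes the Overview names chi-square or Fisher tests. On the continuous side, it says that "differences in continuous variables will be tested using independent group t-tests or Wilcoxon rank-sum tests". Any P-value below 0.05 "will be considered statistically significant". Nothing in this text adds a clinic, repeat-visit or period term to the tests or labels them descriptive.

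Under Study design, "In our study, clinic was the unit of randomization". The same section states that "clinics crossed-over to the intervention condition, three at a time based on their randomization sequence".

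Two later passages use related tests. Under Implementation outcomes analyses, "Paired samples t-tests (or Wilcoxon rank-sum tests) will be used to compare normalization questionnaire scores" between the start and end of the maintenance period. Under Effectiveness outcomes analyses, "Demographic and clinical characteristics between reached/not reached patients will be compared using chi-square" or Fisher tests, with t or rank-sum tests for continuous variables.

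**The concern.** The pre/post and initiated-versus-delayed comparisons are contrasts of the intervention itself. They would put a second set of p-values for the same question beside the model-based results. The tests assume independent observations and no time trend.

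- **Initiated versus delayed.** Whole clinics fall on one side or the other, so between-clinic variation feeds straight into the contrast. The plan's sample size section itself assumes that this variation is not zero.
- **Pre versus post.** The same clinics sit on both sides, so clinic effects largely cancel. What remains is calendar time, which Study design lists among the main limitations of the stepped wedge, plus repeated visits by the same patients.
- **Questionnaire scores.** The rank-sum test compares independent groups. Scores from the same staff at two times call for the signed-rank test.

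At stake is whether a reader of the results tables could take a difference between clinics, or a drift over time, for an intervention effect.

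**Working it through.** The plan attaches no figure to these tests, so there is none to reproduce. The checks use the plan's own inputs where they exist.

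**Inputs from the Sample size calculation section:** ICC 0.01 (given for systolic pressure), 46 patients per clinic per step, SD 20 mmHg, and 1725 patients seen monthly at the smallest clinic. Alpha of 0.05 is taken as two-sided, because the article does not say.

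**1. Initiated versus delayed.** This contrast exists only while some clinics are waiting: 3 against 6, then 6 against 3. With m observations per clinic, the variance is inflated by D = 1 + (m − 1) × ICC, and the true type I error of a nominal 5% test is 2 × [1 − Φ(1.96/√D)].

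- m = 46, ICC 0.01: D = 1 + 45 × 0.01 = 1.45, and the error is 0.104. A simulation of 3 against 6 clinics with a t-test gave 0.106.
- m = 46 with an assumed ICC of 0.02 or 0.05: 0.155 or 0.277.
- Fidelity is counted by patient visit. With m = 1725 (one month's volume at the smallest clinic) and the ICC of 0.01 borrowed: D = 1 + 1724 × 0.01 = 18.24, and the error is 0.646.

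**2. Pre versus post.** Simulated with 9 clinics, 92 patients per clinic on each side (assumed, 2 × 46), SD 20, ICC 0.01, no intervention effect and no repeat visits:

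| Assumed secular fall | Proportion with P < 0.05 |
|---|---|
| 0 mmHg | 0.056 |
| 1 mmHg | 0.18 |
| 2 mmHg | 0.53 |

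A hand check agrees. Each side has 9 × 92 = 828 patients, so the standard error is 20 × √(2/828) = 0.98 mmHg. A 2 mmHg drift is 2.03 standard errors, which crosses 1.96 about 53% of the time. The first row shows that the clustering inflation in step 1 does not carry over to this contrast. Repeat visits are a further fault that these figures leave out.

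**3. Rank-sum on paired scores.** Simulated with an assumed 40 staff and, for power, an assumed shift of 0.4 SD:

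| Correlation within pairs | Type I error, rank-sum | Type I error, signed-rank | Power, rank-sum | Power, signed-rank |
|---|---|---|---|---|
| 0.3 | 0.022 | 0.052 | 0.39 | 0.53 |
| 0.5 | 0.007 | 0.045 | 0.37 | 0.67 |
| 0.7 | < 0.001 | 0.045 | 0.35 | 0.88 |

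The error runs the other way here: too few rejections and lost power.

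**4. Reached versus not reached.** Both groups occur within each clinic, so the formula in step 1 does not apply. Simulation with 9 clinics, ICC 0.01 and a between-clinic SD in reach of 0, 0.5 or 1 logit (assumed) gave type I errors of 0.053, 0.053 and 0.064 at 46 patients per clinic, and 0.057, 0.062 and 0.079 at 184. It reached 0.36 only with 500 patients per clinic, ICC 0.05 and an SD of 1 logit, none of which the article states.

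**The case against.** The strongest reply is that no main conclusion rests on these tests. Fidelity is analysed by mixed log-binomial regression with GEE fallbacks, and systolic pressure by a linear mixed model with clinic and participant random effects. Maintenance of blood pressure measurement and of blood pressure itself is assessed with the same models. The sentence at issue follows directly on the one about summary tables, so the tests may be meant only as unadjusted companions to those tables. The article also does not state the unit of analysis, and some of what the sentence covers is measured per clinic. For the questionnaire, the words on paired t-tests show that pairing is intended, so rank-sum is probably a one-word slip.

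Most of this stands, and it limits the point to the p-values in question. It does not remove it. The article fixes the tests and the 0.05 threshold and does not call the comparisons descriptive. For any outcome recorded per patient or visit, the independence assumption conflicts with the plan's own ICC.

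A reader might go further and infer that the trial's primary results are invalid, or that false-positive rates of 40% to 90% apply throughout. The documents support neither. The primary models account for clinic and period. Rates that high come from the initiated-versus-delayed formula with an assumed ICC or with cluster sizes well above 46. No ICC is given for fidelity, an ICC of 0.05 appears nowhere, and the 1725 counts everyone seen at the clinic, whereas the fidelity population is adults seen in the study triage room. That formula also cannot be carried over to the pre/post or reached comparisons.

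**Conclusion.** The point holds in limited form. As written, the unadjusted tests in the Overview do not give valid p-values for the intervention contrasts. For initiated versus delayed clinics, the type I error is about 10% at the protocol's own ICC and cluster size. The 65% figure for fidelity depends on borrowing the systolic-pressure ICC and on a full month's clinic volume per cluster. For pre versus post, the size depends on the secular trend, which the documents do not give; the range of 18% to 53% illustrates falls of 1 to 2 mmHg. The rank-sum alternative is the wrong test for paired scores, and its consequence is lost power, not false positives. Clustering in the reached/not-reached comparison is a minor matter at the planned sizes. The co-primary and blood-pressure maintenance analyses are not affected. The change is worth making because it needs only wording and prevents conflicting p-values for the same contrast.

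**What to change.** - In the Overview, state that the period-by-period and pre/post comparisons will be reported descriptively without p-values. Alternatively, take any p-value from the planned mixed or GEE model with clinic and period terms, and with a participant term where patients are measured repeatedly.
- Under Implementation outcomes analyses, replace Wilcoxon rank-sum with Wilcoxon signed-rank as the alternative to the paired t-test.
- Optionally, account for clinic when comparing reached and not-reached patients.

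The cost is a few words in the plan. Some p-values disappear from the tables. No data collection, sample size or primary analysis changes.
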